## Abstract

**Background**: Transcranial Direct Current Stimulation (tDCS) is reportedly a potential treatment option for chronic tinnitus. The main drawbacks of previous studies are short term follow up and focusing on the efficacy of single session tDCS. This study aims to investigate the therapeutic efficacy, adverse effects (AEs) and tolerability of repeated sessions of bilateral tDCS over auditory cortex (AC) on tinnitus symptoms

**Methods**: This will be a double-blinded randomized placebo controlled parallel trial on patients (n=90) with intractable chronic tinnitus (> 2 years) randomly divided into three groups of anodal, cathodal, and sham tDCS. In the sham treatment, after 30 sec the device will be turned OFF without informing the patients. The tDCS protocol consists of 10 sessions (daily  20 min session; 2 mA current for 5 consecutive days per week and 2 consecutive weeks) applied through 35 cm
^2^ electrodes. The primary outcome is tinnitus handicap inventory (THI) which will be assessed pre- and post-intervention and at one month follow-up. The secondary outcomes are tinnitus loudness and distress to be assessed using a visual analogue scale (VAS) pre-intervention, and immediately, one hour, one week, and one month after last stimulation. The AEs and tolerability of patients will be evaluated after each session using a customized questionnaire. Possible interactions between the disease features and treatment response will be evaluated.

**Discussion**: To our knowledge this is the first study to investigate the effects of repeated sessions of tDCS on chronic tinnitus symptoms with one month follow-up. In addition, the AEs, and tolerability of patients will be studied. In addition, the possible interactions between the disease specific features including the hearing loss, laterality, type of tinnitus, and treatment response will be evaluated.

**Trial registration**: The study has been registered as a clinical trial in Iranian Registry of Clinical Trial (
IRCT2016110124635N6) on the 01/06/2017.

## Abbreviations

tDCS: transcranial direct current stimulation; AC: auditory cortex; DLPFC: dorsolateral prefrontal cortex; THI: tinnitus handicap inventory; BDI-II: Beck Depression inventory; BAI: Beck Anxiety Inventory; dBHL: decibels hearing level.

## Background

Tinnitus is a subjective auditory phantom perception without an external physical sound source
^1^, which exists in different forms including pulsatile or continuous, buzzing, ringing, hissing, tone, or a combination of them
^2^. It is a relatively common disorder with 10–15% prevalence among adults worldwide. Tinnitus is a debilitating condition which severely affects the quality of life. It is accompanied by different comorbidities such as anxiety, depression, and sleep disturbances
^3^.

 There is no definitive treatment for tinnitus and a large proportion of tinnitus become intractable
^1,
3^. During the recent years, different non-pharmacological techniques have been developed for treatment of chronic tinnitus including cognitive behavioral therapies, hearing aids, neurofeedback, and noise-masking techniques
^4–
6^. Although some of these techniques have shown therapeutic outcomes, the therapeutic efficacies of these techniques are limited and studies to develop more efficient techniques are ongoing.

Transcranial direct current stimulation (tDCS) is a non-invasive neuromodulation technique and recent studies have reported promising therapeutic outcomes in improving cognitive functions in healthy individuals
^7^ as well as symptoms of different neuropsychiatric disorders such as depression
^8^, obsessive compulsive disorder
^9^ auditory-verbal hallucinations
^10^, and chronic pain
^11^. Several studies have investigated the therapeutic efficacy of different tDCS protocols in chronic tinnitus
^11–
15^. Results were in general promising, despite some controversial findings. In treating tinnitus with tDCS, there are two main targets as the site of stimulation including the dorsolateral prefrontal cortex (DLPFC)
^16,
17^, and the auditory cortex
^18–
20^. The neural anomalies, hyperactivity, or maladaptive plasticity of the primary and secondary auditory cortices have been reportedly the main causes of tinnitus loudness and disturbances in non-auditory structures and networks such as anterior cingulate cortex, and particularly DLPFC are the main causes of distress or annoyance experienced in tinnitus
^2,
3,
21^. The main hypothesis for therapeutic application of tDCS in tinnitus is disturbing ongoing abnormal neural activities responsible for tinnitus. According to this approach, the areas involved in the pathophysiology of tinnitus are targeted by tDCS. The other hypothesis of eliciting therapeutic outcomes from tDCS is inducing plastic changes to alter the maladaptive plasticity of the involved regions. The important point for treatment of tinnitus is that there is a large network consisting of different auditory and non-auditory regions with overlapping functions
^22–
24^.

Most of the studies performed to date, have focused on the effects of single tDCS session on tinnitus symptoms, with short term follow ups ranging some hours to some days. To our knowledge, there is no published study investigating the effect of repeated sessions of tDCS over the auditory cortex (AC) on tinnitus symptoms as well as the AEs of and tolerability to the tDCS with one month follow up. This study aims to investigate the effects of repeated sessions of tDCS on tinnitus symptoms with one month follow-up. Our main hypothesis is that repeated sessions will lead to aggregative therapeutic effects on tinnitus. In addition, we want to evaluate possible association between treatment response, and patient's and tinnitus specific characteristics including gender, THI basal score, laterality, tinnitus quality, duration, hearing loss class, etc.

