### Study protocol

This study is a double-blind randomized controlled clinical trial design and patients will be randomly assigned into three groups of anodal and cathodal tDCS and sham tDCS. The random allocation will be performed based on balanced randomization [1:1:1] where the allocation concealment will be applied by random allocation cards using computer-generated random numbers. The three groups will be matched for age, gender, ethnicity, and audiometric main characteristics. To reduce the procedure and subjective bias, the patients, the researchers who will evaluate the outcomes, and the researchers who perform data analyses will be blinded on the type of protocol. In addition, the blinding quality of the study will be assessed after completion of the intervention.

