### Transcranial direct current stimulation protocol

The direct current will be applied through a saline-soaked pair of surface electrodes (35 cm
^2^) and delivered by a tDCS device which is a specially developed, battery-driven, constant current stimulator with a maximum output of 2 mA. The tDCS device used in this study will be an OASIS Pro
^TM^ device by Mind Alive Inc (Edmonton, Alberta, Canada). Anodal and cathodal tDCS groups will consist of daily 20-min sessions of 2 mA current for five consecutive days per week and for 2 consecutive weeks (10 sessions in total). In anodal tDCS, the anode and cathode will be respectively centered over left AC (halfway T3 - F7) and right AC (halfway T4 - F8). In the cathodal tDCS the electrodes position will be reversed where cathode and anode will be respectively centered over left AC (halfway T3-F7) and right AC (halfway T4-F8). The site of electrodes will be selected according to the
International 10-20 electroencephalography system. In the sham tDCS group, the electrode montage will be the same as the anodal tDCS, but the device will be turned off after 30 s without the knowledge of the participant. These parameters for sham stimulation were chosen based on previous reported findings where the perceived sensations of stimulation on the skin, such as tingling, usually disappear in the first 30 s of active tDCS
^23,
26^ (
Table 1).

**Table 1. T1:** Setting for anodal, cathodal, and sham Transcranial Direct Current Stimulation (tDCS).

	Anodal tDCS	Cathodal tDCS	Sham tDCS
Current density	57.1 µA/cm ^2^	57.1 µA/cm ^2^	57.1 µA/cm ^2^
Electrode montage	Anode left (halfway T3 - F7) and cathode right AC (halfway T4 - F8)	Cathode left (halfway T3 - F7) and anode right AC (halfway T4 - F8)	Anode left (halfway T3 - F7) and cathode right AC (halfway T4 - F8)
Duration	20 min	20 min	20 min ^*^

Note: * 30 seconds after the start of the stimulation the device will be turned off without the knowledge of patient.

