### Adverse effects and tolerability

The previous studies on the safety and tolerability of tDCS have shown that the 2 mA current applied in 20 minutes are associated with no serious AEs
^24,
26^. The common reported AEs are itching or tingling sensation, mild headache or fatigue and local burns at the site of stimulation. However, most of the AEs and tolerability assessments have been performed on the tDCS were for single session ranging 20–30 minutes and current of 1 to 2 mA. In our study, we will use repeated sessions of tDCS (2 mA current for 20 minute, total 10 sessions, daily one session, five consecutive days per week and 2 consecutive weeks), thus the reported AEs in the previous studies may be intensified. Therefore, we will assess the AEs using a customized questionnaire (
Supplementary File 1). The questionnaire will be performed during and after each tDCS session to record all the perceived AEs from the patients in all three tDCS groups.

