### Outcomes assessments

The primary and secondary outcomes will be measured in two main time points: pre- and post-intervention. The pre-intervention assessments of the outcomes will be performed at the first day of the intervention before tDCS stimulation (T
_1_). There will be four time points of post-intervention assessments as T
_2_, T
_3_, T
_4_, and T
_5_ corresponding to the immediately after last session, one hour, one week, and one month after last tDCS session.
Table 2 represents the SPIRIT schematic protocol of the study and timing of the assessments.

**Table 2. T2:** Standard Protocol Items: Recommendations for Interventional Trials of this study.

	Enrolment	Allocation	Pre- intervention	Intervention	Post- intervention			
TIME POINT	*-T _1_*	T _0_	*T _1_*		*T _2_*	*T _3_*	*T _4_*	*T _5_*
ENROLMENT:								
Eligibility screen	X							
Informed consent	X							
*Demographic* *information*	X							
Allocation		X						
INTERVENTIONS:								
*real (anodal and* *cathodal) tDCS*								
*Sham tDCS*								
ASSESSMENTS:								
*Neurological* *and audiological* *assessments*	X							
*Hearing loss* *assessment*	X							
*Primary outcome:* *THI*			X		X			X
*Secondary outcomes:* *loudness*			X		X	X	X	X
*Distress*			X		X	X	X	X
*AEs and Tolerability*					X			

Note: THI: tinnitus handicap inventory; AEs: adverse effects, -T
_1_: one month before intervention, T
_0_: one day before intervention, T
_1_: 5 min before intervention, T
_2_: immediately after last session, T
_3_: at hour after last session, T
_4_: one week, and T
_5_: at month after last tDCS session. Real tDCS refers to anodal and cathodal tDCS groups.

***Primary outcome***. Tinnitus handicap inventory (THI) score will be the primary outcome. The THI is a 25-item questionnaire and commonly used as self-reporting inventory for disabling level of tinnitus. The THI items are grouped into three subscales: Functional (11 items), emotional (9 items), and catastrophic (5 items) subscales. Each item is three point Likert type scale with three alternative assessments: yes (4 points), sometimes (2 points), and no (0 point). The questionnaire yields scores for each subscale and a total score that ranges 0 to 100, where higher score means more severe tinnitus or a greater handicap

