***Secondary outcomes***

**Tinnitus loudness and distress**. The tinnitus loudness and distress will be assessed using a numeral 0–10 visual analogue scale rating scale before intervention, and immediately, one hour, one week, and one month after last tDCS session. For tinnitus loudness and distress a 10 percent or 2 point reduction of 0–10 scale will be considered as treatment response
^31,
32^.

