## Blinding assessment

The previous studies have shown that the experience of the sensations induced by tDCS are usually fade out after 30 seconds; thus, we will use this period in the sham tDCS group, to evaluate the blinding quality of the study design, after completion of the intervention we will ask the patients whether they know which type of stimulation, real or sham tDCS, they received. This assessment will be performed after each tDCS session in all groups. 

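### The main hypothesis is an aggregative effect of repeated sessions, but no efficacy rating is taken during the course and no arm gets fewer sessions, so accumulation cannot be told from an effect that one session could have produced.

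*Protocol article*

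**What the plan says.** The Background of the protocol article observes that most earlier tinnitus studies gave a single session, and then states the trial's own hypothesis: "Our main hypothesis is that repeated sessions will lead to aggregative therapeutic effects on tinnitus".

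The design is as follows.

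- **Arms.** Under Study protocol, "patients will be randomly assigned into three groups of anodal and cathodal tDCS and sham tDCS".
- **Course.** Under Transcranial direct current stimulation protocol, the active arms receive "daily 20-min sessions of 2 mA current for five consecutive days per week and for 2 consecutive weeks (10 sessions in total". No arm is described with a single session or a shorter course.
- **Pre-treatment rating.** Under Outcomes assessments, T1 is "performed at the first day of the intervention before tDCS stimulation".
- **Post-treatment ratings.** The same section gives T2 to T5 as "corresponding to the immediately after last session, one hour, one week, and one month after last tDCS session".
- **Measures.** THI, the primary outcome, is taken at T1, T2 and T5. Loudness and distress are rated "before intervention, and immediately, one hour, one week, and one month after last tDCS session". The Intervention column of Table 2 holds no efficacy rating.
- **Data collected per session.** On adverse effects, one section says: "The questionnaire will be performed during and after each tDCS session". On the patient's guess of real or sham stimulation, the article says: "This assessment will be performed after each tDCS session in all groups". Neither measures efficacy.

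**The concern.** Set against single-session studies, an aggregative effect most naturally means benefit that builds up from session to session. It is named as the main hypothesis and is the rationale for giving ten sessions. To examine it, a trial needs either ratings during the course or a comparison arm with fewer sessions. This one has neither.

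Active versus sham at T2 or T5 answers whether ten sessions work. It does not answer whether ten sessions do more than one would have done. A positive result would invite a claim of accumulation that the data cannot support. No analysis plan could repair this afterwards, because the ratings are not scheduled. The article reports allocation as still to come (Trial status), so the schedule could still be changed when it was written.

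**Working it through.** The plan gives no figure on this point, so there is none to reproduce. The check has two parts.

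**1. Count of ratings, from Outcomes assessments and Table 2.**

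| Measure | Before session 1 | Start of session 1 to end of session 10 | Within one hour after session 10 | One week or later |
|---|---|---|---|---|
| THI | 1 (T1) | 0 | 1 (T2) | 1 (T5) |
| Loudness | 1 (T1) | 0 | 2 (T2, T3) | 2 (T4, T5) |
| Distress | 1 (T1) | 0 | 2 (T2, T3) | 2 (T4, T5) |

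The time factor in the planned mixed ANOVA can therefore contain only T1 to T5.

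**2. Can T1 to T5 distinguish accumulation from no build-up?** Take the benefit over sham, in points. These inputs are assumptions: sessions on days 0–4 and 7–11 (one reading of five days a week for two weeks), exponential decay with half-life h days, one month taken as 30 days, and a benefit of 10 points at T2 in both models.

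- *No build-up:* each session resets the benefit to A = 10. At t days after session 10 the benefit is 10·2^(−t/h).
- *Accumulation:* each session adds s, and every contribution decays. At t days after session 10 the benefit is s·Σ 2^(−(11+t−dⱼ)/h), with dⱼ the session days. This factors into s·K·2^(−t/h), where K = Σ 2^(−(11−dⱼ)/h). Setting T2 to 10 gives s = 10/K, so the benefit is again 10·2^(−t/h).

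The two expressions are the same for every t and every h. In the numerical run they differed by at most about 1e-14, which is rounding.

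| Half-life h (days) | K | T2 | T3 | T4 | T5 | After session 1: accumulation | After session 1: no build-up |
|---|---|---|---|---|---|---|---|
| 0.25 | 1.07 | 10 | 8.91 | 0.00 | 0.00 | 9.38 | 10 |
| 1 | 1.95 | 10 | 9.72 | 0.08 | 0.00 | 5.12 | 10 |
| 7 | 6.21 | 10 | 9.96 | 5.00 | 0.51 | 1.61 | 10 |
| 30 | 8.84 | 10 | 9.99 | 8.51 | 5.00 | 1.13 | 10 |

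Columns T2 to T5 hold for both models. Worked example, h = 1: the gaps from session 10 back to each session are 0, 1, 2, 3, 4, 7, 8, 9, 10 and 11 days. The first five terms of K sum to 1 + 0.5 + 0.25 + 0.125 + 0.0625 = 1.9375, and the last five to 1.9375/128 = 0.0151. So K = 1.95 and s = 10/1.95 = 5.12.

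Reading across, T4 and T5 separate a short-lived effect (0.08 or less at one week if h is one day or less) from a lasting one (8.51 and 5.00 if h is 30 days). Reading between the models, nothing at T2 to T5 separates them. A rating just after session 1 does, except when decay is very fast (9.38 against 10 at h = 0.25).

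A rating just before session 5 adds information only if the effect outlasts a day. Under accumulation it is s·Σ 2^(−k/h) for k = 1 to 4; under no build-up it is 10·2^(−1/h). This gives 4.80 against 5.00 at h = 1, and 5.06 against 9.06 at h = 7.

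**The case against.** The strongest reply is that the hypothesis is one loosely worded sentence. Elsewhere the aim is the efficacy, adverse effects and tolerability of repeated sessions with one-month follow-up (Abstract, Background, Discussion), and the sham control, outcomes and time-by-stimulation ANOVA fit that aim. If aggregative means only the summed effect of the course, active versus sham does test it. This stands in part: it is why restating the hypothesis belongs in the fix. It does not remove the point, because the sentence is labelled the main hypothesis and its context is the contrast with single-session work.

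A reader might go further and infer that any benefit found could equally be an acute effect of session 10. The documents do not support that. It applies to T2 and T3 only. Loudness and distress are also rated at one week and one month, and THI at one month, by which time an effect lasting hours or a day would have gone. A reader might also infer that the efficacy comparison is invalid; it is not.

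Two objections to the remedy also stand. A trend in pre-session ratings could come from a slowly developing effect of early sessions, and only an arm with fewer sessions would exclude that; nor was the sample size derived for such contrasts. Also, a form completed at every session cannot be taken for granted. The later section on adverse effects applies the questionnaire after the last session and Table 2 marks it only at T2, whereas the Abstract and the earlier section say each session. The blinding section mentions both completion of the intervention and each session.

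**Conclusion.** The point holds in a limited form. With no efficacy ratings during the course and one course length in all arms, accumulation over ten sessions cannot be distinguished from an effect that a single session could have produced, whatever its duration. T4 and T5 speak to persistence, not build-up. The comparison of the whole course with sham is unaffected.

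The count of zero in-course ratings is read directly from the schedule. The exact agreement of the two models at T2 to T5 rests on their simple form (a common exponential decay, benefits that add or reset), but not on the half-life chosen. The size of the separation after session 1 does depend on the half-life. The matter is worth correcting because the repair is cheap; it does not threaten the trial's main comparison.

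**What to change.** 1. **Restate the main hypothesis** as the effect of the ten-session course versus sham at T2 and T5, and state that accumulation will not be claimed from T1 to T5 alone. This is a wording change.

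2. **Add the existing 0–10 loudness and distress ratings** before and after stimulation at sessions 1, 5 and 10 in all arms. T1 already serves as the rating before session 1 and T2 as the rating after session 10, so 6 − 2 = 4 occasions are new, or 4 × 2 = 8 extra ratings per patient. Rating around all ten sessions is more than is needed.

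3. **Label the analysis secondary and exploratory.** Compare each active arm with sham on the course of the pre-session ratings and on the change across session 1. State that the result can support accumulation but not prove it, because a slowly developing effect of early sessions could look the same and the trial is not powered for these contrasts.

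4. **Settle the per-session forms.** Reconcile the statements on when the adverse-effect questionnaire and the blinding question are given, so that it is clear whether the new ratings can go on an existing form.

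The cost is a slight rating burden, equal in all arms, at visits that patients already attend.

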^29^. The THI is widely used as the primary outcome measure in double-blind trials with a control group to assess the effect of pharmacological or non-pharmacological agents in tinnitus patients. The functional subscale items reflect the effect of tinnitus on mental, social, occupational, and physical functioning. The emotional subscale items probe the individual’s emotional reactions to the tinnitus and the catastrophic response items address whether tinnitus makes the respondent feel desperate, trapped, hopeless or out of control. In this study, the THI will be assessed prior to intervention, and immediately, and at one month after the last tDCS session. Response to treatment is defined as a reduction of equal or more than 20 points in THI score (Pre-treatment THI – Post-treatment THI ≥ 20). This cut-off value for treatment response to tDCS is generally considered as significant clinical improvement in the previous similar studies
^15,
30^. 

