## Statistical assessments

All statistical tests will be performed using
SPSS (V20.0, IBM Corporation, New York, USA). To determine whether the anodal, cathodal, and sham tDCS groups are well-matched in terms of age, sex, quality of tinnitus, tinnitus laterality, THI score, and duration and class of hearing loss, these dependent variables will be compared between the three groups using independent samples t-tests.

For nominal data like gender and class of hearing loss, Chi-square tests will be conducted across groups. Independent sample t-tests were also used to determine if individual baseline measures differed between groups (THI, tinnitus loudness, and distress). Prior to conducting
*t*-tests, Levene’s test for equality of variances was used. In no instance was Levene’s test violated; thus, equality of variances was assumed. The number of female and male participants and the quality of tinnitus symptoms, across each group will be compared using Pearson Chi-square tests. Mixed repeated-measure ANOVAs with the within‐subject factor time and the between‐subject factor stimulation were performed for evaluating changes in THI, tinnitus loudness, tinnitus distress, BDI and BAI scores. For the ANOVAs, sphericity was tested with the Mauchly’s test, and in the event of a violation of Mauchly’s test, the Greenhouse-Geisser correction was applied. In case of significant effects, follow-up post-hoc t-tests were carried out using LSD adjustments for multiple comparisons to examine if tDCS caused a significant difference relative to sham or baseline. An analysis of covariance will be performed with Time as within-subject factor, Stimulation as between-subject factor, and gender, laterality of tinnitus, duration of tinnitus as covariates. In addition, we will calculate Pearson’s correlations between change of THI and tinnitus loudness and distress values from pre- to post-stimulation.

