Finally, we will examine the number of responders versus non-responders under each treatment condition (anodal, cathodal, and sham). This will be accomplished by calculating change scores between the pre-treatment and post-treatment THI values (Pre-treatment – Post-treatment). Responders will be considered individuals who showed reductions in THI score of equal or more than 20 points in the THI score (Pre-treatment THI – Post-treatment THI ≥ 20). For tinnitus loudness and distress a 10 percent or 2-point reduction of 0–10 scale is considered as treatment response. Pearson’s chi-square tests will be used to evaluate whether there are differences in the proportion of responders versus non-responders under each condition. For all statistical tests the P-value < 0.05 is defined as statistically significant level.

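### Baseline THI is to be associated with a response that is itself computed from baseline THI, so regression to the mean alone can make higher baseline look predictive

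*Protocol article*

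**What the plan says.** Three places in the protocol article bear on this.

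- **Background, last paragraph.** The authors wish to "evaluate possible association between treatment response, and patient's and tinnitus specific characteristics including gender, THI basal score". The list of characteristics runs on: "tinnitus specific characteristics including gender, THI basal score, laterality, tinnitus quality, duration, hearing loss class". Baseline THI is thus named as a candidate predictor of response.
- **Outcomes assessments, primary outcome.** "Response to treatment is defined as a reduction of equal or more than 20 points in THI score". The THI has "a total score that ranges 0 to 100".
- **Statistical assessments.** Responders are classified by the same pre-minus-post difference cut at 20 points, and the proportions are compared between anodal, cathodal and sham by chi-square. The analysis of covariance uses "gender, laterality of tinnitus, duration of tinnitus as covariates"; baseline THI is not among them. No term for arm by baseline THI is described.

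The Abstract adds: "Possible interactions between the disease features and treatment response will be evaluated". It lists hearing loss, laterality and type of tinnitus as the features meant, and does not list baseline THI.

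**The concern.** For gender or laterality, a test of association with response has a sensible null value: no association. For baseline THI it does not. The baseline score, with its measurement error and day-to-day fluctuation, enters the response with a positive sign. A patient who happens to score high on the first day tends to score lower later and is more likely to cross the 20-point threshold, whatever was done in between. A test of no association therefore does not test whether the tDCS effect depends on baseline THI.

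There is also a hard limit at the lower end. The article's inclusion criteria give no minimum THI, and a patient entering with a score below 20 cannot fall by 20 points.

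At stake is one reported predictor. Baseline severity could be presented as a marker of who benefits from tDCS when the same pattern would be seen under sham.

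**Working it through.** **Inputs from the article.** Response is pre minus post THI ≥ 20. The THI runs from 0 to 100 with items scored 0, 2 or 4, so totals are even. The significance level is 0.05. The total is 90 in the Abstract and Participants; the Sample size calculation gives 25 per group, 3 × 25 = 75. Both totals are used here.

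**Assumed, because the article does not give them.** THI mean 50 and SD σ = 20 before and after treatment; pre-post correlation ρ from 0.6 to 0.9; no tDCS effect and no effect modification. The article has no figure of its own on this point to reproduce.

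**Step 1: the coupling before the cut.** With equal variances,

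- Cov(pre, pre − post) = σ²(1 − ρ)
- Var(pre − post) = 2σ²(1 − ρ)
- Corr(pre, pre − post) = √((1 − ρ)/2)

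This is 0.45, 0.39, 0.32 and 0.22 at ρ = 0.6, 0.7, 0.8 and 0.9. It is positive for every ρ below 1 and is the same in each arm.

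**Step 2: the coupling after the cut at 20.** Given baseline x, the change has mean (1 − ρ)(x − 50) and SD 20√(1 − ρ²). At ρ = 0.7 the SD is 20 × 0.714 = 14.3. Ignoring rounding to even scores:

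- x = 70: mean change 0.3 × 20 = 6; P(change ≥ 20) = P(Z ≥ 14/14.3 = 0.98) ≈ 16%
- x = 30: mean change −6; P(change ≥ 20) = P(Z ≥ 26/14.3 = 1.82) ≈ 3%

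The cut weakens the link but does not remove it.

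**Step 3: how often this would be declared significant.** Simulated trials (even scores, limited to 0–100), pooled over arms, t-test of baseline THI in responders against non-responders, no effect of any kind:

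| ρ | N = 75 | N = 90 | One arm of 30 |
|---|---|---|---|
| 0.6 | about 71% | about 79% | about 33% |
| 0.7 | about 54% | about 60% | about 21% |
| 0.8 | about 28% | 29–33% | about 9% |
| 0.9 | about 4% | 5–6% | about 1% |

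Repeat runs differ by up to about three points (51% to 54% at ρ = 0.7, N = 75). The nominal rate is 5%, or 2.5% in the direction of higher baseline in responders. At ρ = 0.7 the response rate is about 16% in the upper half of baseline THI and 5% in the lower half, by artefact alone.

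**Step 4: a drop common to all arms.** If every arm, sham included, falls by an assumed 10 points, the N = 75 rates become about 90%, 78%, 57% and 29% in the same order. At ρ = 0.7 response is then 38% in the upper half and 16% in the lower half, still with no tDCS effect.

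**Step 5: the alternative.** Under the same no-effect model, the arm-by-baseline interaction test rejects in about 3–5% of trials, because regression to the mean is common to the arms and cancels.

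**The case against.** The strongest reply is that the test examined here is not in the article. The Background sentence states an aim, the statistical section sets out no analysis of baseline THI against response, and the modelling of an exploratory aim is often left to a fuller document. That is right as far as the choice of test goes, and the percentages above hold only for the test assumed. But the article does fix the pairing: it names both the predictor and the outcome, and they share the baseline score. A different test of association between the two would not remove that.

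A second reply is that the article speaks of interactions, which might mean feature by arm, in which case the artefact cancels against sham. The Abstract and the Discussion, however, write of interactions between features and response, not between features and arm. Baseline THI appears only in the Background, under association.

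A third is that the association is true as description: patients with higher baseline really do fall by 20 points more often. This stands. It becomes an error only when read as prediction of benefit from tDCS, and the article does not commit itself to that reading.

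Three stronger readings are tempting, and the article does not support them.

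- **Near-certain false positives.** Rates of 98%, 94%, 81% and 51% (N = 75, ρ = 0.6 to 0.9) arise for the continuous change, but the article defines response only as the 20-point cut.
- **Patient selection steered to severe tinnitus.** The Discussion hopes to refine the tDCS protocol from interactions with disease features, but neither it nor the Abstract's list of features names baseline THI.
- **A compromised efficacy comparison.** Responder proportions are compared between randomised arms, where this artefact is shared.

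**Conclusion.** The point holds as a limited flaw in a secondary predictor analysis. Associating baseline THI with a response that contains baseline THI can yield an apparent predictor in the absence of any tDCS effect.

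The size depends on assumptions that the article cannot settle: mean 50, SD 20, equal variances, the pre-post correlation, and a pooled two-group comparison. On these, the chance of a spurious finding is large at ρ = 0.6 to 0.7, moderate at 0.8, and about nominal at 0.9 unless the arms share a drop. It is smaller within a single arm. A false finding is therefore a real risk, not a certainty.

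The primary outcome, the arm comparisons and the responder chi-square are not touched, nor are the loudness and distress responses, which do not contain the THI.

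**What to change.** In the Background, take baseline THI out of the characteristics that are simply associated with response. In Statistical assessments, add that:

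- baseline THI will be assessed only through an arm-by-baseline-THI interaction, in a model with post-treatment THI as outcome and baseline THI as covariate, each active arm against sham;
- the result is exploratory and will be reported with its confidence interval;
- an association of baseline THI with response, pooled over arms or within an arm, will not be read as prediction of response to tDCS.

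The responder comparison between arms needs no change. The cost is a few sentences and one extra model on data already collected. The drawback is low power for the interaction with 25 to 30 patients per arm, so a non-significant result will not show that the effect is the same at all baseline scores.
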